#### 2.7.4. MEP Deterioration/Alarm Criteria

Transcranial electrical stimulation: the stimulation threshold for each connected muscle is determined separately. It is defined as the lowest current intensity that is necessary to achieve a muscle action potential of minimally 50 μV. The percentage increase in the stimulation threshold from the baseline is calculated for each muscle and each side of the body. The baseline is determined just after opening of the dura.

An increase in the affected side (arm or leg muscles on the opposite side of the affected brain hemisphere) of more than 20% above the percentage increase in the stimulation threshold of the unaffected side of the body (arm or leg muscles on the side of the body ipsilateral to the affected hemisphere) is considered a significant change and warning signal at the same time. In this case, a resection interruption of 10 min in the area of the motor pathways is recommended. Once the MEP has recovered (difference between the two sides below 20%), the resection can be continued. If the deterioration persists, resection termination in the area of the motor pathways is recommended and the risk of postoperative mild/temporary paresis is pointed out.

If the affected side rises by more than 50% above the percentage increase in the stimulation threshold of the unaffected side of the body, the surgeon is informed about the risk of postoperative severe/permanent paresis.

Direct cortical stimulation: the stimulation intensity is set 2 mA above the stimulation threshold and the percentage change in the measured amplitude of the muscle action potential of the affected muscles (arm or leg muscles on the opposite side of the affected brain hemisphere) is calculated.

A reduction in amplitude by 50% compared to the baseline, or an increase in the stimulation threshold by 4 mA (to maintain the amplitude of the baseline) is considered a significant change and a warning signal at the same time. A resection interruption of 10 min in the area of the motor pathways is recommended. Once the amplitude has recovered (reduction of less than 50% or increase in the stimulation threshold below 4 mA), the resection can be continued. If the deterioration persists, resection termination in the area of the motor pathways is recommended and the risk of postoperative rather slight/temporary paresis is pointed out.

In case of amplitude loss under a maximum stimulation intensity of 25 mA, the surgeon is informed about the risk of postoperative severe/permanent paresis.

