## Abstract

Background: Monitoring of motor function during surgery for supratentorial tumors under general anesthesia applies either transcranial electrical stimulation (TES) or direct cortical stimulation (DCS) to elicit motor-evoked potentials. To date, there is no guideline that favor one method over the other. Therefore, we designed this randomized study to compare between both methods regarding the prediction of postoperative motor deficits and extent of tumor resection. Methods: This is a multicenter (six centers in Germany and one in Switzerland), double blind, parallel group, exploratory, randomized controlled clinical trial. Patients without or with mild paresis, who are scheduled for surgical resection of motor-eloquent brain tumors under general anesthesia will be randomized to surgical resection under TES or surgical resection under DCS. The primary endpoint is sensitivity and specificity in prognosis of motor function 7 days after surgery. The main secondary endpoint is the extent of tumor resection. The study is planned to include 120 patients within 2 years. Discussion: The present exploratory study should compare TES and DCS regarding sensitivity and specificity in predicting postoperative motor deficit and extent of tumor resection to calculate the required number of patients in a confirmatory trial to test the superiority of one method over the other.

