#### 2.7.3. Intraoperative Monitoring

A baseline measurement for each muscle is carried out after dural opening with determination of the stimulation threshold for the transcranial MEP or the stimulation threshold and the amplitude for the direct cortical MEPs. During tumor resection, MEP stimulation is performed at least every two minutes for to the randomized method and every 10 min for the other method. The surgeon is informed if a significant MEP deterioration according to the randomized method occurs, and that in case of persistence of the alteration, a significant deterioration of the postoperative deterioration of motor function is to be expected. At the end of the procedure, a final measurement of the stimulation threshold for the transcranial MEP or the stimulation threshold and the amplitude in the direct cortical MEPs is performed.

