#### 2.13.1. Primary Endpoint

The sensitivity and specificity of the transcranial and direct cortical stimulation with regard to motor deficit at discharge or 7 days after the operation are calculated and compared between the procedures using the Farrington-Manning test. Sensitivity refers to the probability of having a motor deficit at discharge (or 7 days after surgery), after reaching a predefined deterioration of MEP according to the applied alarm criterion during tumor resection. Specificity refers to the probability of not having a motor deficit at discharge (or 7 days after surgery) while not reaching a predefined deterioration of MEP according to the applied alarm criterion during tumor resection. The sensitivity is tested for superiority to a two-sided significance level of 5%; the specificity is tested for non-inferiority with a non-inferiority threshold of 10% with a one-sided significance level of 2.5%. One method is superior to another if it has been possible to demonstrate superiority in sensitivity and non-inferiority in specificity (intersection hypothesis). A correction of control of the type I error is, therefore, not necessary. Despite the conservative design, the main aim of the study is to gain a first understanding of the underlying differences in prognostic sensitivity and specificity between the two procedures.

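### The DCS resume condition is joined by 'or' and so does not undo the DCS alarm: a recording that breaches one criterion meets both

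*Protocol article*

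**What the plan says.** Section 2.7.4 of the protocol article gives a warning rule and a recovery rule for each arm.

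- **DCS alarm:** "A reduction in amplitude by 50% compared to the baseline, or an increase in the stimulation threshold by 4 mA". The threshold criterion carries a qualifier: it is the extra current needed to hold the amplitude at its baseline level. A 10-minute pause near the motor pathways is then advised.
- **DCS recovery:** the sentence opens with "Once the amplitude has recovered" and defines this in parentheses as "reduction of less than 50% or increase in the stimulation threshold below 4 mA". Resection may then go on.
- **DCS persistence:** if the deterioration does not resolve, "resection termination in the area of the motor pathways is recommended and the risk of postoperative rather slight/temporary paresis" is pointed out to the surgeon.
- **TES, for comparison:** the alarm is a side difference in threshold increase of more than 20%. The recovery rule reads "Once the MEP has recovered (difference between the two sides below 20" per cent).

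Section 2.7.3 adds that, for the randomized method, "MEP stimulation is performed at least every two minutes". Section 2.13.1 defines sensitivity and specificity by whether the alarm was reached: "after reaching a predefined deterioration of MEP according to the applied alarm criterion during tumor resection".

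**The concern.** A recovery rule should be the opposite of the alarm it clears. The opposite of *A or T* is *not A and not T*. The article prints *not A or not T*. Where only one DCS criterion is breached, the alarm is still active and the recovery parenthesis is already satisfied by the other criterion. The text then permits resection to continue and, since the deterioration persists, also advises stopping. Taken literally, the stopping advice would be left only for recordings that breach both criteria, although either one is enough to raise the alarm.

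This is the decision point after the 10-minute pause in one of the two randomized arms. Resuming or stopping can bear on motor outcome and on the extent of resection, the main secondary endpoint. The trial runs in seven centres ("six centers in Germany and one in Switzerland"), which should follow the same rule. Under section 2.9 the surgeon does not know which warning criteria are in use, so the surgeon is poorly placed to correct an inconsistent reading by the monitoring staff.

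**Working it through.** The article gives no figure to reproduce here. The check is one of logic.

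**Inputs (section 2.7.4).** Let *a* be the amplitude reduction in % and *t* the threshold increase in mA. A reduction *by* 50% and a rise *by* 4 mA are taken to include the limit itself.

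- Alarm: a ≥ 50 or t ≥ 4
- Resume, parenthesis as printed: a < 50 or t < 4
- Resume, opposite of the alarm: a < 50 and t < 4

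**All four states**

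| a ≥ 50 | t ≥ 4 | Alarm | Resume, printed (*or*) | Resume with *and* |
|---|---|---|---|---|
| no | no | no | yes | yes |
| yes | no | yes | **yes** | no |
| no | yes | yes | **yes** | no |
| yes | yes | yes | no | no |

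As printed, alarm and resume hold together in 2 of 4 states. With *and*, they do so in 0 of 4.

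**Illustrative recordings (assumed values)**

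- 60% reduction, +2 mA: alarm yes (60 ≥ 50); printed resume yes (2 < 4); with *and* no.
- 30% reduction, +5 mA: alarm yes (5 ≥ 4); printed resume yes (30 < 50); with *and* no.
- 60% reduction, +5 mA: alarm yes; printed resume no; with *and* no.
- TES, side difference 25%: alarm yes (25 > 20); resume no (25 is not below 20).

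**Adding the words before the parenthesis.** The sentence first requires that the amplitude has recovered.

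- For 60% and +2 mA, that clause points against resuming while the parenthesis allows it. The sentence disagrees with itself, and the clause can be used to reach the sensible answer.
- For 30% and +5 mA, the amplitude is already within its limit, so clause and parenthesis both allow resumption while the threshold alarm is still active. The clause does not help.

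The second case need not be exotic. The threshold criterion is about holding the amplitude with more current. If the amplitude is read at the raised current, a threshold alarm comes with a preserved amplitude. The article does not say at which current the amplitude is read when recovery is judged.

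**The case against.** The strongest reply is that the truth table tests the parenthesis rather than the sentence. The parenthesis repeats the two alarm criteria in the same order with the direction reversed, so *or* can be read as *respectively*: whichever criterion fired must return within its limit. On that reading neither single-breach example above may resume, which agrees with *and*. A second reply is that *or* may be deliberate: an amplitude drop might count as recovered if the baseline amplitude can be held with less than 4 mA of extra current. Changing the word would then change the DCS intervention. Third, stopping is only advised, stimulation is repeated at least every two minutes, sites rehearse a standardized scenario (section 2.14), and the article condenses a protocol version 3.0 that is not shown and may word the rule more fully.

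Much of this stands as a limit on size. It does not clear the text. The lead-in resolves amplitude-only alarms but not threshold-only alarms. The *respectively* and deliberate readings are both possible, but neither is stated and they give different advice: at 60% and +2 mA the deliberate reading resumes and *respectively* does not. *Respectively* and *and* also part company: if an amplitude alarm clears but the threshold then stands at +5 mA, the first resumes and the second does not, although the new threshold breach should itself raise a fresh warning. Repeated stimulation does not remove the overlap, because a persisting single breach still meets both printed conditions. Section 2.14 does not say that the rehearsed scenario includes single-criterion recovery. Condensing explains what an article leaves out; this rule is printed, and printed wrongly.

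**Conclusion.** The point holds. As printed, the DCS recovery condition does not reverse the DCS alarm, and the two overlap in both single-criterion states. The defect is confined to the DCS arm. The phrasing around the parenthesis suggests a wording slip rather than a chosen rule, but the article does not settle which quantity must recover.

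The effect on patients cannot be quantified, because the article does not report how often only one DCS criterion is breached. It is probably small, given the advisory status of the stop, the frequent repeat stimulation and the site training. Sensitivity and specificity depend on reaching the alarm, so test positivity is not directly affected, and no sample size or error rate changes. This is a minor correction worth making because it concerns a safety-relevant intraoperative rule. The conclusion rests on the article's wording alone; if the full protocol states the rule correctly, only the article needs correcting.

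**What to change.** In the DCS recovery sentence of section 2.7.4, join the two conditions with *and*, and let the sentence refer to the MEP rather than the amplitude alone. For example: once the MEP has recovered (amplitude reduction below 50% and threshold increase below 4 mA), resection can be continued. Resection then goes on only when neither alarm criterion is still met, as in the TES arm.

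If the sponsor intends something else, such as requiring only the criterion that fired to normalise, the sentence should say so. Section 2.13.1 needs no change.

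The cost is a one-sentence edit, essentially one word, and a short note to the sites. The downside of *and* is that some DCS resections may resume slightly later or stop earlier.

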### 2.8. Outcomes

#### 2.8.1. Primary Outcome Measure

Status of motor function at discharge or one week following surgery is the primary outcome measure. It will be assessed using MRC. The change of motor status will be categorized in two groups, improvement or no change, and deterioration of one MRC grade or more.

#### 2.8.2. Main Secondary Outcome Measure

Proportion of remaining tumor will be measured based on pre- and postoperative MRI. Preoperative MRI is performed within 1–2 weeks prior to surgery and postoperative MRT is performed within 72 h after surgery. Thin slice sagittal magnetic resonance T1 contrast imaging in case of enhancing tumors and T2 flair images (minimum 160 slices) are transferred into iPlan 3.0 cranial (BrainLab, Munich, Germany). This software enables a semiautomatic object drawing using the object creation tool. To measure the tumor volume, its area is encircled in each slice with manual correction if required. Afterwards, the tumor volume expressed in ccm, is extracted using the advanced manipulation function. The measurement is performed independently by a neurosurgeon and a neuroradiologist.

### 2.9. Methods against Bias

Selection bias is minimized by randomizing patients, stratified by center, tumor localization and contrast medium enhancement (1:1 treatment ratio). Block randomization with random block length will be performed. Performance bias is reduced by the double-blind study design. Neither the patient nor the neurosurgeon will be aware of the applied warning criteria. Detection bias is reduced by blinding outcome assessors to the data until the end of the study. A statistical analysis plan (SAP) will be written prior to database lock and all results will be published independently of specific findings to minimize reporting bias.

### 2.10. Blinding

Neither the patient nor the neurosurgeon will be aware of the applied monitoring method during tumor resection. If randomized to TES, detection bias resulting from a possible dislocation of the strip electrode will be minimized through regular impedance measurement (every 2 min) and through performing DCS every 10 min. The medical technical assistant who performs the intraoperative monitoring is blinded to the motor outcome and those who assess the motor outcome are blinded to the intraoperative monitoring.

### 2.11. Sample Size

For the calculation of the sample size, it is assumed that both the sensitivity and specificity of transcranial stimulation is 99% [9,10], and a sensitivity of 80% and specificity of 95% for direct cortical stimulation [6,7]. Furthermore, a prevalence of 30% for the occurrence of motor deficits on discharge or 7 days after surgery is assumed. With 110 patients, a 95% confidence interval for the difference in sensitivities would be 29% percentage points wide and 95% confidence interval for the difference in specificities is 13% percentage points wide. This level of accuracy is sufficient for planning a confirmatory study. With a dropout rate of 10%, the aim is to recruit 120 patients. The number of cases was calculated in R 3.6.0.

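### The confidence-interval widths that justify the sample size (29 and 13 points) do not hold for 110 patients split 1:1; the planned comparison gives about 40–47 and 15–22 points

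*Protocol article*

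**What the plan says.** Section 2.11 (Sample Size) of the protocol article sets out the inputs:

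- For transcranial stimulation (TES), "it is assumed that both the sensitivity and specificity of transcranial stimulation is 99" percent.
- For direct cortical stimulation (DCS), "a sensitivity of 80% and specificity of 95% for direct cortical stimulation".
- For the outcome, "a prevalence of 30% for the occurrence of motor deficits on discharge or 7 days after surgery is assumed".

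It then states the precision for sensitivity: "With 110 patients, a 95% confidence interval for the difference in sensitivities would be 29% percentage points wide". For specificity, the corresponding width is given as 13 points. The section judges this precision as follows: "This level of accuracy is sufficient for planning a confirmatory study". The recruitment target is 120, allowing for 10% drop-out, so 110 is the total number of evaluable patients and not the size of one arm.

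Section 2.1 describes a parallel-group trial in which each patient is randomised to TES or DCS. Section 2.9 says that randomisation is "stratified by center, tumor localization and contrast medium enhancement (1:1 treatment ratio"). Section 2.13.1 says that sensitivity and specificity are "compared between the procedures using the Farrington-Manning test", using the alarm criterion applied to the patient.

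**The concern.** Sensitivity is estimated only in patients who develop a deficit, and specificity only in those who do not. In a 1:1 parallel-group trial each arm contributes half of each group. With 110 patients and 30% prevalence, the sensitivity comparison rests on 16 or 17 patients per arm, and a 29-point interval looks too narrow for numbers that small.

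The precision statement is the only justification given for the sample size, and planning a confirmatory trial is the study's declared purpose. If the widths belong to a comparison with twice as many patients per method, the judgement that the precision is sufficient was made on about half the true variance. Whoever plans the next trial would then have estimates much less precise than promised.

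**Working it through.** **Inputs**

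- Rates (2.11): TES 0.99/0.99; DCS 0.80/0.95 (sensitivity/specificity).
- Prevalence 0.30 and N = 110 in total (2.11); allocation 1:1 (2.9), so 55 per arm.
- Deficits per arm: 55 × 0.30 = 16.5. Non-deficits per arm: 55 × 0.70 = 38.5.
- Counted over all 110 patients: 33 deficits and 77 non-deficits.

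**Attempt to reproduce 29 and 13 with 55 per arm**

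The full Wald width is 2 × 1.96 × √[(p₁(1−p₁) + p₂(1−p₂))/n].

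- Sensitivity: 2 × 1.96 × √[(0.0099 + 0.16)/16.5] = 0.398.
- Specificity: 2 × 1.96 × √[(0.0099 + 0.0475)/38.5] = 0.151.

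Other 95% intervals were computed at the same rates, for the 1:1 split and with all 110 patients counted for each method. Widths are in percentage points, sensitivity / specificity:

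| Interval | 55 per arm (16.5 / 38.5) | 110 per method (33 / 77) |
|---|---|---|
| Wald | 39.8 / 15.1 | 28.1 / 10.7 |
| Agresti-Caffo | 44.4 / 19.5 | 30.1 / 12.4 |
| Farrington-Manning score | 46.1 / 22.2 | 30.0 / 13.5 |
| Miettinen-Nurminen score | 47.0 / 22.4 | 30.2 / 13.6 |
| Newcombe | 47.2 / 22.3 | 31.5 / 13.7 |
| Wald, continuity-corrected | 51.9 / 20.3 | 34.2 / 13.3 |
| **Stated in 2.11** | **29 / 13** | **29 / 13** |

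No interval in the 55-per-arm column gives the stated pair. Rounding to whole patients does not help: the lowest widths found were 36.2 (17/17 vs 14/17) and 13.8 (39/39 vs 37/39), both Wald with an observed 100% in the TES arm. A different confidence level does not explain the pair either: a 90% Wald interval gives 33.4 and 12.7.

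**Which sample size do the stated widths fit?**

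Solving the Farrington-Manning interval for n:

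- 29 points needs 34.9 deficits per method: 34.9/0.30 ≈ 116 patients per method.
- 13 points needs 81.3 non-deficits per method: 81.3/0.70 ≈ 116 patients per method.

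The two widths agree on about 116 per method, or about 232 in a parallel-group trial. With 110 per method the score interval gives 30.0 and 13.5, close to the stated figures. A plausible cause is that the total of 110 was used as the size of each arm. That is an inference, because the R routine is not given.

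**Consequence under the plan's own assumptions**

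- The score interval for the sensitivity difference (expected 19 points) runs from about −3 to +43 points with 16.5 deficits per arm. With 33 per method it runs from about +6 to +36.
- The exact power of the two-sided 5% sensitivity comparison (pooled score statistic) is 35% with 16 deficits per arm and 40% with 17. With 33 it would be 83%.

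**Drop-out**

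120 × 0.90 = 108, not 110; conversely 110/0.90 = 122.2. At 54 per arm (16.2 deficits, 37.8 non-deficits) the Wald widths are 40.1 and 15.3 and the Farrington-Manning widths 46.6 and 22.5.

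**The case against.** **The calculation may have been within-patient.** Section 2.7.2 installs both methods in every patient. Section 2.7.3 stimulates with the randomised method at least every 2 minutes and with the other every 10, so all 110 patients could supply data on both. A paired Wald interval on 33 and 77 patients gives about 27–28 and 9–11 points. Tango's paired score interval, over the possible range of within-patient dependence, gives 28.7–31.1 and 11.9–13.7, ranges that contain 29 and 13. The stated widths could therefore be right for a paired analysis.

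This stands as a possible explanation of the figures but does not rescue the text. No section plans a paired comparison, section 2.13.1 counts only the applied criterion, and the Farrington-Manning test is for independent groups. The two methods are also sampled at different frequencies, and the surgeon is told only of alarms from the randomised one. On this reading, 2.11 and 2.13.1 contradict each other.

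**The specificity gap depends on the method.** Averaged over simulated outcomes with 55 per arm, the mean Wald width is about 13.8 points, close to the stated 13. This is fair: the specificity shortfall ranges from under 1 point to about 9, depending on an interval method that is not named. The low end comes partly from arms with observed 100% specificity, where Wald performs poorly. The same averaging gives about 38 points for sensitivity, still about 9 above the stated width.

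**The trial is exploratory and sized on precision.** Misstated widths do not bias the estimates, no threshold for sufficient precision is given, and no power is claimed. All true. The power figures above only illustrate the loss of information. But a design justified by precision alone needs that precision stated correctly. The drop-out discrepancy is minor and the conclusion does not depend on it.

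**Conclusion.** The precision statement is wrong for the comparison that the article describes. On its own assumptions, with 55 evaluable patients per arm, the expected 95% interval for the sensitivity difference is about 40–47 points wide against the stated 29, and for specificity about 15–22 against 13. The sensitivity discrepancy holds for every interval tried; the size of the specificity discrepancy depends on the method. The planned between-arm comparison carries about half the information that the stated widths imply.

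This rests on 110 being the total, on 1:1 allocation with independent groups, and on the stated rates and prevalence. Why 29 and 13 were obtained cannot be settled from the article. Either the total was used as the arm size, or a paired calculation was made that does not match the planned test. Both need correction.

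**What to change.** Rewrite section 2.11 for the planned comparison:

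1. Give the numbers per arm: 55 evaluable (54 if 120 are recruited and 10% drop out), with about 16 deficits and 38 non-deficits.
2. Give expected 95% interval widths of about 40–47 points for sensitivity and 15–22 for specificity, naming the interval method. The score interval consistent with the Farrington-Manning test gives about 46 and 22.
3. Reconsider the sentence that calls this precision sufficient, and say what the confirmatory trial can be planned on with intervals of this width.
4. If 29 and 13 came from measuring every patient with both methods, say so, state the assumed within-patient dependence, and replace the independent-groups test in section 2.13.1 with a paired one.
5. Reconcile 110 with 120 and 10% drop-out.

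The cost is a less favourable precision statement in the protocol and consistent wording in the SAP. No additional patients are required.
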